## Abstract

**Background:**

Patients with chronic disease represent an at-risk group in the face of the COVID-19 crisis as they need to regularly monitor their lifestyle and emotional management. Coping with the illness becomes a challenge due to supply problems and lack of access to health care facilities. It is expected these limitations, along with lockdown and social distancing measures, have affected the routine disease management of these patients, being more pronounced in low- and middle-income countries with a flawed health care system.

**Objectives:**

The purpose of this study is to describe a protocol for a randomized controlled trial to test the efficacy of the Adhera® MejoraCare Digital Program, an mHealth intervention aimed at improving the quality of life of patients with chronic diseases during the COVID-19 outbreak in Paraguay.

**Method:**

A two-arm randomized controlled trial will be carried out, with repeated measures (baseline, 1-month, 3-month, 6-month, and 12-month) under two conditions: Adhera® MejoraCare Digital Program or waiting list. The primary outcome is a change in the quality of life on the EuroQol 5-Dimensions 3-Levels Questionnaire (EQ-5D-3L). Other secondary outcomes, as the effect on anxiety and health empowerment, will be considered. All participants must be 18 years of age or older and meet the criteria for chronic disease. A total of 96 participants will be recruited (48 per arm).

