### Sample size

Sample size calculation was done using G*Power [24], based on the primary endpoint. Specifically, sample size was calculated for a mixed ANOVA design, with the between effects being the experimental condition (2 groups) and the within-effects being the different time points. As we were interested in the interaction between experimental group and time effect, 8 measurements were specified (2 groups x 4 time points). With a power of 80%, and an alpha level = .05, and an expected moderated effect size of d = .50 according to similar studies [25], the required sample size is 74 participants (37 per condition). Taking into account a potential dropout of 20% according to literature [26, 27], this study will recruit a total of 94 participants (47 per condition).

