The general practitioners and specialists participating in the study will identify patients belonging to the high-risk group for CDs. Once identified, the physicians will make a face-to-face appointment with the potential candidates to explain the conditions of participation in the research study. Those interested in participating will sign the informed consent form and complete a brief questionnaire to verify compliance with the inclusion criteria: men and women; 18 years and older; CD diagnosis (i.e., cardiovascular disease, chronic obstructive pulmonary disease, diabetes, hypertension, and cancer); no severe psychiatric comorbidities (i.e., substance dependence, bipolar affective disorder, obsessive compulsive disorder, psychotic illness); and own an Android smartphone. Physicians participating in the study will have access to the patient’s medical history to check for the presence of a diagnosis of mental illness and the presence of severe psychiatric comorbidity. Subsequently, those who meet the criteria for participation in the study will complete the measures corresponding to the baseline through the *LimeSurvey* platform via a link that will be sent to the participant’s email address. Afterwards, participants will be randomized to one of the two conditions (intervention or control). An independent researcher from Valencia University will generate a permuted block randomization with fixed and concealed block length (20 participants per block), and with an allocation ratio of 1:1, using a computerized random number generator (Random Allocation Software 2.0 [30]). For methodological reasons, participants will not be blind to the condition. All patients will be assessed at 1-, 3-, 6- and 12-months from the time of randomization via the *LimeSurvey* platform. Fig 1 shows SPIRIT flow diagram of the study.

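### The abstract plans to recruit 96 (48 per arm) but the sample-size section plans 94 (47 per arm), and only 94 follows from the stated inputs

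*Protocol article*

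**What the plan says.** The article states the number to recruit in two places.

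- **Abstract, Method:** "A total of 96 participants will be recruited (48 per arm". No derivation is given.
- **Sample size section:** "the required sample size is 74 participants (37 per condition" before dropout. Then, "Taking into account a potential dropout of 20% according to literature", the text concludes that "this study will recruit a total of 94 participants (47 per condition".

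The section Study population, recruitment, and eligibility criteria fixes randomisation "with an allocation ratio of 1:1", so both totals are meant to split evenly, and each agrees with its own per-arm figure. Neither is described as an update, an approximation or a count of a different population.

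**The concern.** Both statements are about the same quantity, the number of people to enrol, and they cannot both be the plan. A slip in one digit is an unlikely explanation, because the total and the per-arm figure differ together (96 with 48, 94 with 47).

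The planned size tells the team when recruitment is complete, and it is the benchmark against which a reader later judges whether the trial met its plan. With two published figures, enrolment could close at either and be described as on target. A fixed number matters a little more than usual here. Participants know their allocation, there is no formal data monitoring committee, the committee that monitors recruitment consists of the protocol's authors (Data monitoring), and the principal investigators hold the complete data set before the main results are published (Access to data). Nothing in the article suggests that anyone would use this to choose a stopping point, but a single prespecified number would remove the question. The abstract is also the part most likely to be read and extracted, and it carries the figure that has no derivation.

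**Working it through.** **Inputs, all from the Sample size section unless noted**

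- Evaluable participants required: 74, or 37 per arm
- Dropout: 20%
- Allocation: 1:1 (Study population section)
- Stated totals to recruit: 94 (Sample size section) and 96 (abstract)

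**Step 1. Reproduce the Sample size section's total.** The number to recruit is n / (1 − dropout), rounded up.

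- Per arm: 37 / (1 − 0.20) = 46.25, rounded up to 47. Total 2 × 47 = 94.
- From the total: 74 / 0.80 = 92.5, rounded up to 93, or 94 once made even for 1:1 allocation.

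Both routes give 94, so this figure is reproduced exactly.

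**Step 2. Try to reach 96.**

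| Route | Calculation | Total |
|---|---|---|
| Multiplying by 1 + dropout (a common mistake), on the total | 74 × 1.2 = 88.8 | 89 |
| The same, per arm | 37 × 1.2 = 44.4, up to 45 | 90 |
| Filling whole blocks of 20 | 5 × 20 | 100 |
| 38 evaluable per arm, 20% dropout | 38 / 0.8 = 47.5, up to 48 | 96 |
| 37 evaluable per arm, 22% dropout | 37 / 0.78 = 47.4, up to 48 | 96 |

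Starting from 37 per arm, rounding up gives 48 only when dropout lies above 1 − 37/47 = 21.3% and at or below 1 − 37/48 = 22.9%. Neither a base of 38 nor a dropout in that range appears in the article.

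**Step 3. Size of the difference.**

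- 96 − 94 = 2 participants, 1 per arm; 2/94 = 2.1%.
- Expected completers at 20% dropout: 94 × 0.8 = 75.2 and 96 × 0.8 = 76.8. Both exceed 74.
- Power: take the article's own premise that 74 completers give 80% at a two-sided 5% level (sidedness is not stated), and use a normal approximation. The standardised effect at 74 is then 1.960 + 0.842 = 2.802, and it scales with the square root of the number of completers.
  - 94 recruited: 2.802 × √(75.2/74) = 2.824; power Φ(2.824 − 1.960) = 80.6%.
  - 96 recruited: 2.802 × √(76.8/74) = 2.854; power Φ(2.854 − 1.960) = 81.4%.
  - Difference: about 0.8 percentage points.

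**The case against.** The strongest reply is that this is an editorial slip of no consequence. The two totals differ by 2, both cover the required 74 after dropout, and no estimate or test depends on which is used. The Sample size section is the dedicated place for the calculation and the abstract sentence has no support, so a careful reader can tell which figure was derived. No interim efficacy analysis is described, and a window of two participants is too narrow for meaningful optional stopping. Randomisation in fixed blocks of 20 also makes per-arm precision partly notional. Since 94 = 80 + 14 and 96 = 80 + 16, an incomplete fifth block could leave splits as uneven as 50:44 or 50:46.

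Most of this stands as a limit on the size of the problem. The stopping risk is a possibility only, and the dropout arithmetic in the Sample size section is correct. What is wrong is that the abstract contradicts it. None of this reconciles the two figures.

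A separate caution concerns the base of 74. With f = d/2 = 0.25, 5% alpha, 80% power and an assumed correlation of 0.5 between repeated measures (the article gives none), 74 is reproduced as a between-groups main effect with 2 groups and 8 measurements per person. It is not reproduced as the group-by-time interaction that the text names. On the same assumptions that interaction needs 24 for 4 time points or 22 for 5. So saying that 94 follows means only that it follows from the stated 74 and 20%; it does not endorse the 74. That question neither explains nor removes the conflict between 94 and 96.

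**Conclusion.** The concern holds. The article states two incompatible recruitment targets, and only 94 (47 per arm) follows from its own inputs of 37 evaluable per arm and 20% dropout. The figure of 96 in the abstract is unsupported as written. The contradiction rests on no assumption; the power difference of about 1 percentage point rests on accepting that 74 completers give 80% power. The effect is small and does not threaten the trial's validity, but the planned size is a figure the trial relies on and should be corrected.

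**What to change.** State one recruitment target in the abstract and the Sample size section, and check that the registry entry, which was not available for this review, agrees. On the calculation given, that target is 94 (47 per arm), and the abstract should be changed to match. If 96 is the intended number, the Sample size section should instead show the evaluable number and dropout rate that produce it. If the base of 74 is itself revised, the single target should be rederived from the new base. The cost is one corrected number, or one added line of calculation if 96 is kept; the design and analysis are unaffected.

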**Conclusions:**

It is expected that the Adhera® MejoraCare Digital Program will show significant improvements in quality of life and emotional distress compared to the waiting list condition. Additionally, it is hypothesized that this intervention will be positively evaluated by the participants in terms of usability and satisfaction. The findings will provide new insights into the viability and efficacy of mHealth solutions for chronic disease management in developing countries and in times of pandemic.

**Trial registration:**

ClinicalTrials.gov NCT04659746.

## Introduction

The arrival of the COVID-19 has significantly impacted people’s mental health worldwide [1]. Evidence has shown that feelings of fear, uncertainty and loneliness, and symptoms of stress, anxiety and depression, are very prevalent in most individuals after the COVID-19 outbreak [2]. In Paraguay’s context, infection cases increased rapidly as in the rest of the world [3]. The study conducted by Torales et al. [4] showed that most of the Paraguayan population showed a moderate level of self-perceived stress, particularly in women, singles, and those who reported a pre-existing mental disorder such as depression or anxiety.

People with chronic disease (CD) (e.g., hypertension, diabetes, cardiovascular disease, cancer) are one of the groups most vulnerable to COVID-19 infection [5] and associated mental health problems [6]. Moreover, the implementation of the lockdown measures has impacted these people’s lifestyle [7, 8]. The current health crisis has exacerbated difficulties in accessing medical services and treatment, impacting these diseases’ clinical course [9]. Thus, there is a need to develop and disseminate innovative online care tools to engage at-risk populations in effective CD management during the COVID-19 era.

Throughout this pandemic, the integration of digital health solutions (e.g., smartphones) into CD management has improved access to quality and affordable care for patients by facilitating treatment adherence and behavioral changes [10]. Considering the increasing use and access to the Internet and mobile technology by the Latin American population, digital health could help overcome the healthcare gap in this population [11]. However, it remains challenging to address existing barriers to implementing and disseminating effective mHealth initiatives to improve the most vulnerable communities’ physical and mental health in a low-resource context [12].

Scientific literature suggests that mHealth solutions, including mobile applications (apps), help manage a CD [13, 14], including its possible comorbidity with other psychological problems [15]. In particular, the changes in CD patients’ lifestyle through the use of the mHealth apps are remarkable, mainly in adherence to regular exercise, healthy diet and body weight [16]. Besides, a growing body of research examines apps’ possibilities to improve quality of life or well-being in CD patients through different theoretical approaches (e.g., positive psychology), yielding promising results [17, 18].

Despite the wide variety of apps available for the management of CD during the COVID-19 situation, their quality and efficacy are generally unknown [10, 19]. Therefore, more studies are needed to rigorously ensure the efficacy, efficiency and cost-effectiveness of mHealth solutions. In this regard, this paper aims to describe a protocol for a randomized controlled trial (RCT) to test the efficacy of the Adhera® MejoraCare Digital Program to improve the quality of life of CD patients during the COVID-19 situation in Paraguay, comparing to the waiting list (WL) condition. Adhera® MejoraCare Digital Program (Adhera Health, Inc., Palo Alto, CA) is an mHealth intervention focused on tailored education, behavior change and emotional well-being. We hypothesize that a) Adhera® MejoraCare Digital Program will improve quality of life compared to WL condition 1 month after baseline, and this result will be maintained over time (3-, 6- and 12-month follow-ups); b) Adhera® MejoraCare Digital Program will show significant improvements in emotional distress (anxiety, depression and stress) 1 month after baseline compared to the WL condition, and these results will be maintained over time (3-, 6- and 12-month follow-ups); c) participants in this intervention will positively value the mHealth solution in terms of usability and satisfaction; and d) variables such as self-efficacy and health empowerment will show significant relationships with the change in the quality of life outcome, being significant predictors.

## Material and methods

### Research design

A two-arm RCT will be carried out with repeated measures (baseline, 1-, 3-, 6-, and 12-month follow-ups) and two conditions: Adhera® MejoraCare Digital Program and WL group. The study will be conducted following the CONSORT statement (Consolidated Standards of Reporting Trials, http://www.consort-statement.org) [20] and CONSORT-EHEALTH guidelines [21] and the Recommendations for Interventional Trials (SPIRIT) [22, 23].

### Sample size

Sample size calculation was done using G*Power [24], based on the primary endpoint. Specifically, sample size was calculated for a mixed ANOVA design, with the between effects being the experimental condition (2 groups) and the within-effects being the different time points. As we were interested in the interaction between experimental group and time effect, 8 measurements were specified (2 groups x 4 time points). With a power of 80%, and an alpha level = .05, and an expected moderated effect size of d = .50 according to similar studies [25], the required sample size is 74 participants (37 per condition). Taking into account a potential dropout of 20% according to literature [26, 27], this study will recruit a total of 94 participants (47 per condition).

### Study population, recruitment, and eligibility criteria

The study will be carried out in the region of Itapúa (Paraguay), in collaboration with the Regional Hospital of Encarnación, where the Autonomous University of Encarnación has its Research and Documentation Center.

The department of Itapúa is located in the extreme south of Paraguay, and its capital is the city of Encarnación. According to the last national census [28], the population of the department of Itapúa is 625.096 inhabitants, which represents 8.5% of the total population of the country. Specifically, 85% of the area of the Encarnación district is rural. Regarding education, illiteracy rate is 7%, and there is a difference between the illiteracy rate between the rural and urban population of 18% and the average year of schooling is 8 years. Regarding the use of digital devices, technology is increasingly being incorporated into the lives of Paraguayans. Specifically, 65% of people use the Internet in Itapúa [29].

The general practitioners and specialists participating in the study will identify patients belonging to the high-risk group for CDs. Once identified, the physicians will make a face-to-face appointment with the potential candidates to explain the conditions of participation in the research study. Those interested in participating will sign the informed consent form and complete a brief questionnaire to verify compliance with the inclusion criteria: men and women; 18 years and older; CD diagnosis (i.e., cardiovascular disease, chronic obstructive pulmonary disease, diabetes, hypertension, and cancer); no severe psychiatric comorbidities (i.e., substance dependence, bipolar affective disorder, obsessive compulsive disorder, psychotic illness); and own an Android smartphone. Physicians participating in the study will have access to the patient’s medical history to check for the presence of a diagnosis of mental illness and the presence of severe psychiatric comorbidity. Subsequently, those who meet the criteria for participation in the study will complete the measures corresponding to the baseline through the *LimeSurvey* platform via a link that will be sent to the participant’s email address. Afterwards, participants will be randomized to one of the two conditions (intervention or control). An independent researcher from Valencia University will generate a permuted block randomization with fixed and concealed block length (20 participants per block), and with an allocation ratio of 1:1, using a computerized random number generator (Random Allocation Software 2.0 [30]). For methodological reasons, participants will not be blind to the condition. All patients will be assessed at 1-, 3-, 6- and 12-months from the time of randomization via the *LimeSurvey* platform. Fig 1 shows SPIRIT flow diagram of the study.

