**Fig 1 pone.0273290.g001:**
[figure not shown]
SPIRIT flow diagram: Schedule of enrollment, interventions and assessments. CFS, Computer Fluency Scale; EQ-5D-3L, EuroQol 5-Dimensions 3-Levels Questionnaire; GAD-2, Generalized Anxiety Disorder Questionnaire-2; PHQ-2, Patient Health Questionnaire-2; PSS-4, Perceived Stress Scale-4; GSES-12, General Self-Efficacy-12; HES, Health Empowerment Scale; SUS, System Usability Scale; TUQ, Telehealth Usability Questionnaire; MAUQ, mHealth App Usability Questionnaire; and CSQ, Client Satisfaction Questionnaire. *This instrument will be administered in the Adhera MejoraCare condition.

The intervention or follow-up will be discontinued if: a) the participant withdraws consent; b) the RCT is discontinued (e.g., due to poor patient recruitment, technological problems with the app that delivers the intervention); and c) the principal investigator or project administrator determines the need to discontinue the RCT (e.g., due to ethical and privacy issues, funding problems).

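### The block length is called concealed but is a single fixed number printed in the protocol: an avoidable weakness in an unblinded trial, not a shown breach of allocation concealment

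*Protocol article*

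**What the plan says.** The section on study population, recruitment and eligibility describes the procedure as "permuted block randomization with fixed and concealed block length (20 participants per block), and with an allocation ratio of 1:1". An independent researcher generates the list by computer. No stratification is mentioned, and no rule is given for an incomplete last block. The same section states: "For methodological reasons, participants will not be blind to the condition".

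Physicians identify candidates, see them face to face and take consent. The baseline questionnaire follows through an emailed link, and randomization comes after that. The Measures section makes the EQ-5D-3L, a self-report instrument, the primary outcome. The Data monitoring section gives the task of monitoring recruitment to a trial management committee made up of the protocol's authors.

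On numbers, the Sample size section says "this study will recruit a total of 94 participants (47 per condition", while the Abstract says "A total of 96 participants will be recruited (48 per arm". The text after Fig 1 allows follow-up to end if "the RCT is discontinued (e.g., due to poor patient recruitment", among other reasons.

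**The concern.** The description contradicts itself: the length is called concealed, and the number follows in brackets. With a fixed length, one number describes the whole list. Once ten participants in a block have gone to one arm, the rest of that block must go to the other, and anyone keeping count can know this before the next patient is approached.

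What is at stake is selective enrolment. If a recruiter can foresee the next allocation, the choice of whom to invite, or when, can depend on it. Masking of participants is not available here as a second safeguard, and the outcome is the participant's own rating. The control arm also receives nothing for a year, which gives a well-meaning physician a motive to steer. The authors who monitor recruitment know the length as a matter of course.

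**Working it through.** **Inputs.** Block length 20, so 10 + 10 under 1:1 allocation (recruitment section). Planned total 94 (Sample size section) or 96 (Abstract). Before dropout, "the required sample size is 74 participants (37 per condition". Dropout 20% (Sample size section).

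**1. The plan's own figure.** 37 / (1 − 0.20) = 46.25, rounded up to 47 per condition, so 94 in total. This reproduces. The 47 is therefore a rounded recruitment target for each arm.

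**2. Allocations that can be known with certainty.** Take a block of 2m with m per arm, and a person who knows the length and all allocations so far. An allocation is certain when it and all later slots of the block belong to the same arm. For the last L slots this has probability 2·C(2m − L, m) / C(2m, m). Summing over L = 1 to m gives an expected 2m/(m + 1) certain allocations per block.

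- For m = 10: 20/11 = 1.82 per block. A simulation of 50,000 blocks gave 1.818.
- Four full blocks: 4 × 1.82 = 7.3.
- At 94 participants, the 14 slots used of a fifth block add 2 × (C(13,10) + C(12,10) + C(11,10) + C(10,10)) / C(20,10) = 2 × (286 + 66 + 11 + 1) / 184,756 = 0.004, which is nothing.

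As a share of all allocations this is 1/(m + 1): 1/11 = 9% for blocks of 20, but 1/3 = 33% for blocks of 4. A length of 20 is thus a fairly protective choice among fixed lengths.

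**3. Balance at the planned total.** 94 = 4 × 20 + 14. The first four blocks give 40:40. The number in one arm among the first 14 slots of a 10 + 10 block is hypergeometric.

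| Split (either direction) | Probability |
|---|---|
| 47:47 | C(10,7)² / C(20,14) = 14,400 / 38,760 = 0.372 |
| 46:48 | 0.488 |
| 45:49 | 0.130 |
| 44:50 | 0.011 |

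Exact equality is missed with probability 1 − 0.372 = 0.63. The arms differ by 2 or less with probability 0.372 + 0.488 = 0.86. The expected absolute difference is 1.6 and the maximum is 6. At 96 the last block supplies 16 slots, and P(48:48) = C(10,8)² / C(20,16) = 2,025 / 4,845 = 0.418, so equality is missed with probability 0.58.

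**4. Effect on power.** The 74 is reproduced by a between-groups repeated-measures F test with f = 0.25, 8 measurements and an assumed correlation of 0.5 between measurements. Under that model, after 20% dropout, power is 0.814 at 47:47 and 0.812 at 44:50. The most extreme split costs about 0.2 percentage points.

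**5. Early stopping.** A difference of 10 requires stopping exactly after the tenth slot of a block with all ten in one arm: 2 / C(20,10) = 2 / 184,756, about 1 in 92,000.

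**The case against.** The strongest reply is that knowing the length reveals nothing without the running sequence, and the article does not give recruiters that sequence. Several general practitioners and specialists recruit. Consent and the eligibility check come before an emailed baseline, so list order need not follow the order in which any one physician enrols. Installation instructions and access codes go from the research team to the participant by email. The list is made by an independent researcher. Concealed may simply mean concealed from recruiting staff during enrolment, and the article does not say whether enrolment was still open when it appeared.

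Most of this stands. A reader might infer that concealment has failed, but the document does not support that. The figure of about 7 is the most that a fully informed counter could be certain of on average, and not an estimate of what any physician knew. What remains is that the article does not say from whom the length is concealed, prints it, and leaves it known to the group that monitors recruitment.

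A reader might also infer that the procedure fails to deliver the stated 47 per condition and that this is a design error. That does not follow. The plan promises a 1:1 ratio and a rounded target, and the departures are small and harmless.

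**Conclusion.** The point holds as a minor but real weakness. The plan describes as concealed something that it publishes, and uses one fixed length where varied lengths would protect better. For someone with full knowledge of length and sequence, the exposure is about 1.8 certain allocations per block, roughly 7 of 94. This assumes one unstratified list and a counter who sees every allocation in order. The documents establish neither that such a person exists among the recruiters nor that any enrolment was influenced.

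The mismatch between blocks of 20 and a total of 94 or 96 needs no separate correction. The disagreement between 94 and 96 is a different matter and should be settled in its own right.

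**What to change.** For slots not yet allocated, have the independent researcher generate the list with several moderately large even block sizes in random order. Withhold the sizes from recruiting physicians and from those monitoring recruitment until enrolment closes. Replace the description of the block length in the recruitment section with a statement that sizes vary, that they are undisclosed, and from whom. If recruitment has ended, report the actual split and state who knew the block length and who could see the allocations as they accrued.

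One tempting repair should be avoided: four blocks of 20 followed by one of 14. It would guarantee 47:47, but the lengths stay fixed, and the certain allocations for an informed counter rise from 7.3 to 7.3 + 14/8 = 9.0. It would remove a harmless imbalance and make the list more predictable.

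The cost is minutes of work and a one-line amendment. The one drawback is that short blocks are easier to guess, so very small sizes should be left out of the mix.
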